### Data collection schedule

With the exception of the tobacco and alcohol use questionnaires and EHR data, all other data measures are collected seven times: at baseline and at two, four, six, 12, 18, and 24 months. Tobacco and alcohol use are asked at baseline, 12, and 24 months, and medical record data are pulled at baseline and every 6 months. See Table 2 for the schedule of data collection, and the following Demographics, Outcome Measures, and Utilization/Intervention Data sections for more detail.

**Table 2 Tab2:** Outcome Measures Utilized in PRIMIER

Measure	Frequency						
Demographics	Baseline	2 months	4 months	6 months	12 months	18 months	24 months
Age	●	●	●	●	●	●	●
Race	●	●	●	●	●	●	●
Ethnicity	●	●	●	●	●	●	●
Sex	●	●	●	●	●	●	●
Education	●	●	●	●	●	●	●
Marital status	●	●	●	●	●	●	●
Employment status	●	●	●	●	●	●	●
Insurance status	●	●	●	●	●	●	●
Likelihood of insurance billing	●	●	●	●	●	●	●
Household income	●	●	●	●	●	●	●
Self-reported height	●	●	●	●	●	●	●
Self-reported weight	●	●	●	●	●	●	●
Opioid medication use	●	●	●	●	●	●	●
Fruit and vegetable Intake	●	●	●	●	●	●	●
Tobacco and alcohol use	●				●		●
Exercise	●	●	●	●	●	●	●
Patient-Reported Outcome Measures							
PROMIS-29	●	●	●	●	●	●	●
PROMIS-1 (Quality of Life)	●	●	●	●	●	●	●
Perceived Stress Scale (PSS-4)	●	●	●	●	●	●	●
Patient Activation Measure (PAM)	●	●	●	●	●	●	●
Utilization/Intervention							
Patient Self-Report							
Experience with IM services	●	●	●	●	●	●	●
IM service utilization	●	●	●	●	●	●	●
Chronic pain	●	●	●	●	●	●	●
Primary condition being treated	●	●	●	●	●	●	●
Primary symptom being treated	●	●	●	●	●	●	●
Change in symptoms	●	●	●	●	●	●	●
Medical Records							
IM Clinic Visits							
Dates of all appointments to the IM clinic	●			●	●		●
IM services received	●			●	●		●
Diagnostic codes (ICD-9)	●			●	●		●
Billing codes (CPT)	●			●	●		●
Any Clinic Visit							
Height	●			●	●		●
Weight	●			●	●		●
Pain	●			●	●		●
Lipid Panels	●			●	●		●

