### Data analyses

#### General statistical considerations

All subjects who complete baseline measurements, ≥1 follow-up visit at a BraveNet clinic, and who are followed for at least 6 months in the study will be included in statistical analyses. Counts and percentages will be reported on categorical variables whereas continuous variables will be expressed as means and standard deviations (SDs) and/or medians (25^th^ and 75^th^ percentiles). The Wilcoxon rank-sum test or Chi-square test (Fisher’s exact as appropriate) will be used to quantify comparisons as deemed necessary.

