### Future data analysis

In observational studies like PRIMIER, there is no treatment randomization. Therefore, to minimize the effects of potential stable moderators (e.g., sex), channeling bias, and/or time- varying confounders, a Marginal Structural Model (MSM) approach will be utilized to analyze the final PRIMIER database. An MSM analysis is a weighted repeated measures approach using IM modality as a time-varying covariate as well as accounting for baseline characteristics. Weights produce a pseudo-population with a balance in both time-invariant and time-varying covariates, allowing for causal treatment comparisons using standard repeated measures models. The weighting will also be adjusted to account for missing data, providing validity under missing at random or missing completely at random. In order to incorporate adjustment for patients with missing visits, the same weight approach is used. However, instead of using a flag to designate IM modality, a flag denoting whether the patient remained in the study is used. The final weight for each patient’s observation is computed by multiplying the IM modality selection weights and the censoring weights. There are four major components which need to be computed/assessed to perform a MSM analysis: 1) weight estimates for each subject visit adjusting for IM modality, 2) weight estimates for each subject visit adjusting for study discontinuation, 3) an a priori chosen vector of time-independent variables, such as baseline characteristics, 4) an a priori chosen IM modality or set of IM modalities which will be assigned as the “treatment of interest” and tracked throughout time. Adjusted mean outcomes by study time as well as resulting F-test p-values will be reported by outcome measure.

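### The missing-data weight models dropout only, so the MAR validity credited to it does not cover surveys skipped by participants still in the registry

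*Protocol article*

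**What the plan says.** All the relevant statements stand in one paragraph of the protocol article, under Future data analysis.

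- Claim: "The weighting will also be adjusted to account for missing data, providing validity under missing at random or missing completely at random".
- Purpose: "In order to incorporate adjustment for patients with missing visits, the same weight approach is used".
- Indicator: in place of the modality flag, "a flag denoting whether the patient remained in the study is used".
- The same component in the numbered list: "weight estimates for each subject visit adjusting for study discontinuation".
- Final weight: "computed by multiplying the IM modality selection weights and the censoring weights". There is no third factor.
- Outcome model: the weights are described as "allowing for causal treatment comparisons using standard repeated measures models". Whether that model is fitted by likelihood or by estimating equations is not stated.

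Two other sections set the context. Under Data collection schedule, "all other data measures are collected seven times: at baseline and at two, four, six, 12, 18, and 24 months". Under General statistical considerations, the analysis set is "All subjects who complete baseline measurements, ≥1 follow-up visit at a BraveNet clinic, and who are followed for at least 6 months". Nothing there requires any particular follow-up survey to have been completed.

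**The concern.** The purpose and the claim are about missing data in general, and about missed visits in particular. The indicator is about leaving the study. The two coincide only if every missed survey is followed by no further surveys.

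Participants complete the surveys themselves, online or on paper, at seven time points, while utilization data come separately from records. Someone can therefore be in the registry and in the analysis set with a gap in the middle. For that person the flag reads as remained at every visit. The missing outcome contributes nothing to the model, and no similar participant who did answer is weighted up to stand in for it.

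At stake are the planned reports of adjusted mean outcomes by study time and, under a further condition, the comparisons between modalities. A reader of the results would take the weighting to have dealt with non-response under MAR, when it would have dealt with one form of it.

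**Working it through.** **1. Text check.** No figure in the article can be reproduced on this point, so the first step is to compare what the weight should cover with what its definition covers.

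| Pattern after baseline | Remained flag | Reweighted? |
|---|---|---|
| Answers at 2 and 4 months, then leaves | changes to left | yes |
| Skips 4 months, answers at 6 | remained throughout | no |
| Skips 4 and 12 months, answers at 18 | remained throughout | no |

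The article names the component in three ways (remaining in study, censoring, discontinuation), and all three describe the first row only. The planned sensitivity analysis by 75, 50 and 25 % of surveys completed restricts the sample by completion. It does not reweight for skipped surveys.

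**2. Visit means, illustration.** Every input is an assumption: T-score SD 10, correlation between visits 0.7, true mean change 0, and skipping that depends only on the observed prior score (MAR). In standardized units Y1 = 0.7·Y0 + e and P(skip) = expit(a + ln(OR)·Y0), with a set to give the stated skip rate. Bias is 10 × the mean of the observed Y1.

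| Skipped | OR 1.5 per SD | OR 2.0 per SD |
|---|---|---|
| 10 % | -0.27 | -0.45 |
| 20 % | -0.54 | -0.89 |
| 30 % | -0.82 | -1.32 |
| 40 % | -1.07 | -1.74 |

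Weighting by the inverse probability of being observed at the visit brings every cell to within 0.03 of 0.

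**3. The same set-up using the observed prior score** (20 to 40 % skipped):
- regression of Y1 on Y0 among responders, evaluated at the full-sample mean of Y0: 0.00 to 0.02, so no material bias;
- responders' simple change from baseline: +0.25 to +0.77, the opposite sign.

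The sign change follows from the model. If the observed mean of Y1 is -1.74, the same responders' mean of Y0 is about -1.74 / 0.7 = -2.49, and their change is about -1.74 + 2.49 = +0.75.

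**4. Modality contrasts, illustration.**
- With a true effect of -2.0 and skipping unrelated to modality, the crude unweighted contrast was -2.01 to -2.06, so bias was at most 0.06.
- A second simulation made skipping depend on modality and on an observed severity covariate. Its assumed inputs were N = 10,000, six follow-ups, a fixed binary modality, dropout of about 5 % per visit and a true effect of -2.0.

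| Skipped | No weights | Remained-in-study weight | Plus per-visit observed weight |
|---|---|---|---|
| 11 % | -2.48 | -2.49 | -1.98 |
| 24 % | -3.08 | -3.09 | -1.97 |
| 38 % | -3.70 | -3.74 | -1.98 |
| 40 %, stronger dependence on severity | -5.16 | -5.20 | -1.99 |

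With the dropout weight the bias is -0.49, -1.09, -1.74 and -3.20 (each estimate minus -2.0), no better than with no weights. With no skipping, both weighted estimates are -2.02. The sizes are products of the assumed mechanism. The pattern is what carries over: a dropout weight does not act on skipped surveys, and a per-visit weight does.

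**The case against.** **The flag is not defined visit by visit.** The article speaks of weights for each subject visit and introduces the step as an adjustment for missed visits, so the authors may have meant that a survey was completed at that visit. A condensed article also leaves coding detail to the SAP, which is not shown. This has some force. But the wording points consistently to dropout, and an analyst following it would code dropout. The mismatch lies between a stated rule and its stated purpose, so it is not merely a missing detail.

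**The outcome model may already protect the estimates.** A reader might infer that validity under MAR fails for the whole analysis. The article does not support that. It does not name the estimation method, and a likelihood-based model that conditions on the relevant observed scores could absorb much or all of the problem, as step 3 shows. What stands is narrower: the article credits MAR validity to the weighting, and the weighting as specified does not deliver it for skipped surveys.

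**The direction is not known.** A reader might infer a bias toward improvement because sicker participants skip. No skip mechanism is given, and step 3 shows that the sign reverses between a visit mean and a responders' change score. Modality contrasts need skipping to depend on modality as well.

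**The frequency is not known.** A reader might take the 75/50/25 % subsets as evidence that intermittent gaps will be common. The article ties those subsets to retention, and dropout alone would produce the same percentages. They show that incomplete response is expected, not which kind.

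**It is early.** The section concerns the final database of a registry planned for 10 years. That makes the change easier to adopt and does not remove the reason for it.

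**Conclusion.** The point holds as a mismatch between claim and method. The weights are said to handle missed visits with validity under MAR, but the indicator specified handles study discontinuation only. Surveys skipped by participants still in the registry are not reweighted, and nothing else described in the article reweights for them.

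The consequence is conditional. Adjusted visit means can be biased if skipping depends on observed prior scores or other measured covariates that the outcome model does not condition on. Modality contrasts can be biased if skipping depends on modality as well. No size or direction can be attached to the planned analysis, because the article gives neither the skip mechanism nor the estimation method. The illustrations range from essentially no bias to 1.74 points on a visit mean, and up to 3.20 points on a contrast under the strongest assumed dependence. They show how the weights behave and do not predict the registry's results. If skipping is MCAR, no such bias is expected; if the model is likelihood-based and conditions on the relevant observed scores, bias may be small or absent.

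**What to change.** Add a visit-response factor to the final weight. Among participants still in study at each scheduled visit, model whether the PRO was observed (yes/no) from baseline variables, last observed PROs, prior modality and prior response pattern. The final weight for an observation becomes:

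modality weight × discontinuation weight × 1 / P(PRO observed at this visit | still in study, history).

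Count a survey as missing only if it was due by the data cut, so that participants enrolled later are not treated as non-responders.

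If the existing flag was meant to denote survey completion at the visit, reword it and the descriptions of the component as discontinuation and censoring to match. If the authors prefer to keep a dropout weight alone, limit the MAR statement to dropout and state how intermittent gaps are handled.

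The cost is about a sentence of text, one more response model within the same weighting step, and slightly more variable weights. The change can be made before the final database is analysed.

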**Discussion:**

As the PRIMIER registry grows, we anticipate that our results would provide an indication of the promise of PBRN research efforts in IM. Analyses will incorporate a large sample of participants and an expected 10-year observation period and will provide the ability to evaluate the effect of IM on outcomes for specific clinical populations and specific IM interventions or combinations. As such, PRIMIER will serve as a national platform for future evaluations of IM best practices.

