### Patient-reported outcome measures

PRIMIER uses the PROMIS-29 instrument as the core PRO measure along with the Perceived Stress Scale-4 (PSS-4) [13] and the Patient Activation Measure (PAM) [14].

Created with funding from the National Institutes of Health, the PROMIS suite of PRO instruments provides clinicians and researchers access to efficient, valid, and responsive self-reported measures of health, including symptoms, function, and well-being. The PROMIS-29 instrument includes four-item short forms covering seven distinct domains including physical function, anxiety, depression, fatigue, pain intensity and pain interference, satisfaction with social role, as well as sleep disturbance. Questions are answered using standard one through five Likert scales. The PROMIS-29 has been validated as performing as well as a variety of legacy PRO measures [15], and the four-item subscales for depression and anxiety have been found to have good internal reliability among chronic pain patients [16]. A crosswalk has been developed and validated between PROMIS Pain Interference and the Pain Interference subscale of the Brief Pain Inventory [17], and between the PROMIS Fatigue short form and the Modified Fatigue Impact Scale [18]. PROMIS Depression has also been cross-walked with several common depression measures (e.g., Beck Depression Inventory-II and Center for Epidemiologic Study-Depression) [19]. In addition to the PROMIS-29, we include one PROMIS question to assess global quality of life.

The Perceived Stress Scale-4 (PSS-4) is a brief, validated, and widely used psychological instrument for assessing a participant’s perception of stress level. Based on an original 14-item scale [20], the PSS-4 consists of four questions to measure the degree to which participants perceive situations in their lives as stressful [13]. It includes questions related to perceived unpredictability, uncontrollability, and overload. This short version is recommended for a brief assessment when respondent time is limited. Participants choose responses ranging from never (0) to very often (4) with a total score ranging from 0 to 16. A recent study on the PSS-4 reconfirms its reliability [21].

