As our sample size increases and the proportion of those completing long term follow-up assessments grows, we will be able to evaluate the impact of IM on pain scores in subgroups including but not limited to: sex, BMI < 30 vs BMI ≥ 30, and <40 on the PROMIS Depression Subscale vs ≥40 on PROMIS Depression Subscale. The potential of the varying impacts of IM on subgroups will be assessed by including interaction terms, i.e., subgroup by IM, in the MSM model. In the case that the interaction terms are statistically significant, separate MSM analyses will be performed within each subgroup. Also, the weight estimates for each subject visit will be computed adjusting for dose of modality or modalities of interest (e.g., acupuncture or IM physician visit) instead of IM modality in the MSM analysis. Accounting for modality dosing by visit over the course of the study may potentially create more robust weight estimates for each subject by providing more information than just a binary response variable.

Sensitivity analysis to assess the impact of retention rate will be performed on pre-specified subgroups of subjects who completed:75 % of surveys over the study period50 % of surveys over the study period25 % of surveys over the study period

All analyses will be conducted using SAS (Cary, NC).

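### Separate subgroup estimates are made conditional on a significant interaction, over a subgroup list left open, so the subgroup differences that reach that stage are selected and biased away from zero

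*Protocol article*

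**What the plan says.** The section Future data analysis in the protocol article plans to look at pain scores across "subgroups including but not limited to: sex, BMI < 30 vs BMI ≥ 30, and <40 on the PROMIS Depression Subscale" (the other side of that cut being 40 or more). Differences in effect between subgroups "will be assessed by including interaction terms, i.e., subgroup by IM, in the MSM model". The next sentence sets the rule at issue: "In the case that the interaction terms are statistically significant, separate MSM analyses will be performed within each subgroup".

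Three other statements determine how often the rule is applied:

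- The outcome is given in the plural, as pain scores. The section Patient-reported outcome measures lists two pain domains in the core instrument: "pain intensity and pain interference, satisfaction with social role, as well as sleep disturbance".
- The IM modality, or set of modalities, of interest is to be chosen in advance, but the article does not name it.
- A dose-based version of the weights is also planned, with acupuncture and IM physician visits as examples.

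No significance level is given for the interaction test. The article does not say how a non-significant interaction will be reported.

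**The concern.** Testing the interaction before looking within subgroups is sound. The difficulty is the use of its p-value to decide which subgroup estimates are produced. This has three consequences:

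- **False triggers.** Every added subgroup factor or pain score is another chance for the rule to fire when the effect of IM is the same everywhere. An open list puts no limit on the number of chances.
- **Selection.** Estimates that appear only because the interaction passed a threshold are on average too far from zero.
- **Asymmetry.** Factors that miss the threshold get no separate analysis, although a non-significant interaction is compatible with a sizeable difference when precision is low.

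The abstract says that the analyses "will provide the ability to evaluate the effect of IM on outcomes for specific clinical populations and specific IM interventions or combinations", and the main Discussion asks whether depressive symptoms change the effectiveness of mind/body interventions. Estimates of effect modification are thus part of what the registry is meant to supply to later studies. Those studies would be planned on inflated differences if only the selected ones were carried forward.

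**Working it through.** **Stated figure.** The article gives no power, significance level or error rate for the interaction tests, so there is nothing to reproduce.

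**Inputs from the article.** Three named subgroup factors, two pain domains in the PROMIS-29, and an anticipated enrolment of about 10,000 (Screening procedures and enrollment).

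**Inputs assumed.** A two-sided 5% level, with 10% shown as a range; the correlations between tests; and the power of the interaction test.

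**Step 1: chance of at least one spurious trigger with no heterogeneity.** For k independent tests at level α this is 1 − (1 − α)^k.

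| Tests | k | α = 0.05 | α = 0.10 |
|---|---|---|---|
| 3 factors, 1 pain score, 1 modality | 3 | 1 − 0.95³ = 14.3% | 1 − 0.90³ = 27.1% |
| 3 factors, 2 pain domains, 1 modality | 6 | 1 − 0.95⁶ = 26.5% | 1 − 0.90⁶ = 46.9% |

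Correlation lowers these values somewhat. At α = 0.05, simulation gives 13.6% for k = 3 with pairwise correlation 0.3, and 12.6% with 0.5. For k = 6, assumed correlations of 0.7 between the two pain domains and 0.1 between factors give 23%. The range with two pain domains is therefore about 23% to 27%.

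The probability grows with the list. Under independence at 5% it first exceeds one half at k = 14, where 1 − 0.95¹⁴ = 51.2%.

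**Step 2: exaggeration among interactions that pass.** Let θ be the true interaction divided by its standard error, and let the estimate Z be normal with mean θ and variance 1. The mean exaggeration is E(|Z| given |Z| > 1.96) / θ.

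| Assumed power | θ | Mean \|Z\| if significant | Ratio |
|---|---|---|---|
| 20% | 1.115 | 2.515 | 2.26 |
| 30% | 1.435 | 2.593 | 1.81 |
| 50% | 1.960 | 2.758 | 1.41 |
| 80% | 2.802 | 3.152 | 1.12 |
| 90% | 3.242 | 3.436 | 1.06 |

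If the true interaction is zero, those that pass still show a mean |Z| of 2.34.

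**Step 3: where power might lie.** As an illustration only, assume that 20% of patients use the modality, that the subgroups split 30/70, that the true interaction is 0.2 SD, and that each patient contributes one effective observation. The standard error is √(1 / (n × 0.2 × 0.8 × 0.3 × 0.7)) = √(1 / (0.0336 n)).

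- n = 1,250: SE 0.154, power 25%, ratio 2.0.
- n = 2,500: SE 0.109, power 45%, ratio 1.5.
- n = 10,000: SE 0.055, power 96%, ratio 1.03.

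The bias is thus material at low effective sample sizes and negligible if all 10,000 were fully informative.

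**The case against.** The strongest reply has four parts.

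- **An interaction test first is a recognised safeguard.** It is better than comparing within-subgroup p-values. This stands, and the fix keeps the test.
- **The registry is exploratory.** The Discussion speaks of exploring later hypotheses and of preliminary information for research proposals, and an open list fits that aim. This lowers the seriousness. It does not justify filtering estimates by p-value, because exploratory work depends most on seeing all estimates with their intervals.
- **The article is condensed.** A significance level or a multiplicity rule may sit in an analysis plan that is not shown, so their absence is no fault here. This stands. The point rests on two things the article does state: the trigger and the open list.
- **The size of the bias is not established.** The effective n, modality use and subgroup split in the illustration are assumptions, and the planned model uses up to seven assessments per patient. This stands for the size. It does not remove the direction of the bias.

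A reader might also infer more than the text supports. The article does not say that the tests are unadjusted, that non-significant interaction results will be withheld, or that they will be read as showing equal effects. It makes only the separate MSMs conditional. Nor does it commit to repeating the interaction tests for several modalities or with dose-based weights: the two modalities appear as examples, and dose is introduced as a way to compute weights.

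**Conclusion.** The concern holds in a limited form. A stated rule filters the separate subgroup analyses on statistical significance, and the subgroup list has no end. At an assumed 5% level with no heterogeneity, the chance of a spurious trigger is about 14% for what is named, with one pain score and one modality, and about 23% to 27% with two pain domains. It increases with each further factor.

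It would go too far to say that a spurious subgroup finding is likely. That needs about 14 independent tests, or more if they are correlated, which the open wording allows but the article does not plan.

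The selected differences are biased away from zero, but no single factor of exaggeration can be given. It runs from about 2.3-fold at 20% power to 1.1-fold at 80%, and the article gives nothing from which power could be derived. The defect is worth correcting because the correction is almost free. It does not undermine the registry's design.

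**What to change.** In Future data analysis, delete the sentence that makes separate subgroup MSMs depend on a significant interaction. Replace it with three statements:

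1. Sex, BMI and PROMIS Depression are the pre-specified subgroup factors.
2. For each factor, the interaction estimate and both subgroup-specific effects are reported with 95% confidence intervals from the single MSM, whatever the p-value.
3. Any further subgroup is labelled exploratory and carries no significance claim.

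A multiplicity adjustment across the listed interactions is optional in a registry with these aims. As an illustration, Bonferroni over three tests uses 0.05 / 3 = 0.0167 per test and lowers the chance of any false interaction from 14.3% to 1 − (1 − 0.0167)³ = 4.9%. It would not remove the selection; only reporting every listed estimate does that.

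The cost is a change of wording and a few more tabulated contrasts from a model that is fitted anyway.

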### Screening procedures and enrollment

Potential participants receive PRIMIER enrollment information either from clinic or research staff. Patients who decide to participate in PRIMIER log onto the PRIMIER website and electronically enroll directly into the registry. Online registrants are able to provide informed consent upon opening the first screen on their initial visit to the website. If they do not have computer access or are uncomfortable with technology, patients may provide informed consent and complete the survey questionnaire by pen and paper. Following enrollment in PRIMIER, PRO measures are obtained at 2-month intervals for the first 6 months, then every 6 months through the end of year two. This information is combined with data extracted from the participants’ EHR. We anticipate approximately 10,000 participants to be enrolled in PRIMIER.

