### Utilization/intervention data

In addition to providing PRO measures, participants report the primary condition(s) or symptom(s) for which they are receiving treatment and the type of IM practitioner from whom they are receiving care based on questions from the National Health Interview Survey. At each data collection point, patients are asked to rate or describe their change in symptoms, etc. since beginning care at the IM clinic [27]. Patients report whether they are experiencing chronic pain, defined as 4 or greater on an 11-point visual analog scale. PRIMIER also collects information on what IM interventions patients have utilized in the past 6 months. Utilization of IM treatments is captured through two methods: 1) as reported by the study participants using patient visit questionnaires; and 2) as reported by the sites through an electronic or paper medical record extraction process. Each site abstracts the following data points from their participant’s electronic medical and administrative records: dates of all appointments to the IM clinic, IM services received, diagnostic codes (International Classification of Diseases-9: ICD-9) associated with each IM visit, and billing codes (Current Procedural Terminology: CPT) associated with each visit. These data are encrypted and sent electronically to the BraveNet data coordinating center. Additional data fields will be added from patient visits to any clinic (i.e., not limited to IM clinic visits) as relevant to specific studies of interest, for example, height, weight, pain, and lipid panels.

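### The stated retention sensitivity analysis compares completion subgroups that never depart from missing at random, so agreement across them cannot rule out or size bias from outcome-dependent attrition

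*Protocol article*

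**What the plan says.** Four statements in the protocol article bear on this point.

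- **Survey schedule** (Data collection schedule): apart from tobacco and alcohol items and record data, measures are "collected seven times: at baseline and at two, four, six, 12, 18, and 24 months".
- **Analysis set** (General statistical considerations): subjects who "complete baseline measurements, ≥1 follow-up visit at a BraveNet clinic, and who are followed for at least 6 months in the study" are analysed. The rule names a clinic visit and a length of follow-up. It does not name a follow-up survey.
- **Main model** (Future data analysis): a marginal structural model whose modality weights are multiplied by censoring weights. For the latter, "a flag denoting whether the patient remained in the study is used". The weighting is described as "providing validity under missing at random or missing completely at random".
- **Retention check** (end of Future data analysis): "Sensitivity analysis to assess the impact of retention rate will be performed on pre-specified subgroups of subjects who completed" 75%, 50% or 25% of surveys over the study period. The text does not write *at least*, does not say whether baseline counts as a survey, and does not name the model to be fitted in the subgroups.

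**The concern.** The censoring weights protect the result if dropout can be explained by what has been recorded. The remaining risk is dropout that depends on scores nobody saw, for example patients who stop answering because a modality did not help them. A sensitivity analysis on retention is most useful if it probes that risk.

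The stated check moves in another direction. Each step up keeps people with more complete response, and all steps start from a set that has already lost those not followed for six months. The missing-data assumption is the same at every step. If the three results agree, attrition has not been shown to be harmless. If they differ, the difference may come from the extra selection. The Discussion expects the registry to identify the most effective modalities as participation and retention grow, so false reassurance about attrition would bear directly on the main use of the data.

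**Working it through.** The article gives no figure to reproduce here. The check turns the thresholds into survey counts and asks what each step can reveal.

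**1. Thresholds as counts.** The schedule gives 7 surveys including baseline, or 6 follow-up surveys. The number needed is the threshold times the number of surveys, rounded up, reading each threshold as *at least*.

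| Threshold | 7 surveys (baseline counted) | 6 surveys (follow-up only) |
|---|---|---|
| 25% | 1.75, so 2 | 1.5, so 2 |
| 50% | 3.5, so 4 | 3 |
| 75% | 5.25, so 6 | 4.5, so 5 |

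**2. The 25% step.** With baseline counted, baseline plus any one follow-up survey is 2/7 = 28.6%, which passes. Baseline alone is 1/7 = 14.3%, which fails. If only follow-up surveys count, one survey is 1/6 = 16.7%, which fails. There are 2^6 = 64 possible follow-up response patterns. The number that the 25% step removes depends on how the entry rule is read:

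| Entry rule read as | Baseline counted | Follow-up only |
|---|---|---|
| No follow-up survey needed | 1 of 64 | 7 of 64 |
| At least one follow-up survey | 0 of 63 | 6 of 63 |
| Month-6 survey needed | 0 of 32 | 1 of 32 |

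These are counts of patterns, not of people; the article gives no frequencies.

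**3. The 50% step.** Surveys at months 0, 2, 4 and 6 give 4/7 = 57.1% (or 3/6 = 50% on follow-up surveys). Either count passes with nothing recorded after month 6 of a 24-month schedule.

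**4. The 75% step.** A perfect responder has 5/7 = 71.4% at month 12 and 6/7 = 85.7% at month 18. On follow-up surveys the figures are 4/6 = 66.7% and 5/6 = 83.3%. Either way the step is out of reach before month 18.

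**5. Does agreement exclude bias?** An illustration with assumed parameters, none taken from the article:

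- 400,000 patients in two equal groups, with a true difference of 0.
- Baseline SD 1, individual change SD 0.5, residual SD 0.5, so the month-12 SD is √(1 + 0.25 + 0.25) = 1.22.
- Permanent dropout at each survey with log-odds −1.4, plus the current score in one group only.
- Unweighted comparison at month 12.

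The subsets with at least 2, 4 and 6 surveys gave differences of −0.71, −0.71 and −0.81. All three are wrong by more than half an SD (0.71/1.22 = 0.58). With dropout completely at random, or with the same outcome-dependent dropout in both groups, all three were within 0.01 of zero.

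The first two values are equal by construction. If dropout is permanent, anyone observed at month 12 has already completed 5 of 7 surveys, so the 25% and 50% steps hold the same people at that visit.

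**6. Is a shift evidence of bias?** Not by itself. If dropout is permanent, everyone in the 6-of-7 subset is present through month 18. Censoring weights re-estimated there equal 1 up to that visit, so the adjustment in the main model is switched off. In a second illustration, dropout in one group depended only on the last observed score, so missing at random held and the true difference was 0. The fully weighted month-12 estimate was 0.01. The 6-of-7 subset gave −0.14 with the same weights and −0.42 without them. The sizes depend on assumed parameters; only the direction matters. Here the main result was valid and the sensitivity result was not.

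**The case against.** The strongest reply is that the article claims only to assess the impact of retention rate, not to test missing at random. Comparing results across levels of completeness is a reasonable way to see whether they depend on it. That much stands: a shift across the steps, such as −0.71 to −0.81 above, is a signal worth looking at. A reader might infer that the check can show nothing about missing data, and that goes too far. It cannot exclude or size bias from outcome-dependent dropout, and it cannot separate that bias from selection.

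Three other strong readings are also unsupported.

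- **The 25% step excludes nobody.** This holds only if baseline counts and every analysed patient has a follow-up survey. The entry rule asks for a clinic visit, and visits come from the medical record ("dates of all appointments to the IM clinic, IM services received, diagnostic codes"), so a patient with only the baseline survey can be analysed and fail this step.
- **Dropouts never enter.** Those who leave after six months can be in the 25% and 50% subsets. The people missing from every step are those not followed for six months, and the entry rule removes them.
- **Recent enrollees always fail the 75% step.** The model is planned for the final database of a registry expected to run ten years, so most or all surveys may be due by then. The problem arises only at an earlier cut.

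It is also fair to say that a condensed article may leave fuller missing-data plans to documents not shown. The absence of a departure-from-MAR analysis is therefore not the finding. The finding is that the one analysis the article does fix is poorly suited to its stated purpose. That the main model is refitted in each subgroup, and that the subgroups are nested, are readings of a text that states neither.

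**Conclusion.** The concern holds in a limited form. The stated completion subgroups condition on response after baseline within an already restricted set, and none varies the assumption behind the censoring weights. Agreement across them cannot rule out or size bias from outcome-dependent attrition, and a shift is ambiguous.

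The two lower thresholds also discriminate weakly. The 25% step removes few or no response patterns (0 to 7, depending on the reading), and the 50% step can be met with no data after month 6.

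This rests on reading the thresholds as *at least*. The 25% result also depends on whether baseline counts and on whether the entry rule needs a survey, neither of which the article settles. The argument about missing at random depends on neither. How large any attrition bias would be cannot be said from the article, because it gives no dropout rates. This is a worthwhile, inexpensive improvement and does not invalidate the main model.

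**What to change.** 1. Add a sensitivity analysis that departs from missing at random: delta-adjusted multiple imputation, or a pattern-mixture tipping point. Worsen unobserved patient-reported scores in steps until the conclusion changes, and report the delta at which it does.
2. Let the delta differ between modality groups. In the illustration, the same outcome-dependent dropout in both groups left the difference near zero, while dropout in one group alone did not.
3. Include participants with baseline data who were lost before six months. Appointment and service data from the record can supply modality history for those who still attended.
4. In the imputed data keep the modality weights and drop the censoring weights, so that missing surveys are not handled twice.
5. Keep the completion groups as description only. Define them as at least a stated share of the surveys due at the data cut, say whether baseline counts, and name the model.

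The cost is plan wording, modest extra programming and the need to justify a delta range in advance. No new data are needed.
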